### Standardized therapy and trial interventions

The site of hand-port placement will be randomized. All other intraoperative and perioperative treatments are standardized procedures. Prophylactic antibiotic therapy and use of intravenous or oral analgesic agents to relieve postoperative pain will be administered according to our kidney transplantation manual [21].

According to the randomization arm, hand-port placement and hand insertion will be via a midline periumbilical or Pfannenstiel incision. HALDN with a periumbilical incision will be performed by positioning the donor in a left/right lateral decubitus position. A 5-mm laparoscope port will be placed at the midclavicular line in the left/right upper quadrant (two finger breadths below the costal margin), and one working instrument (12 mm) will be placed at the level of the umbilicus to the left/right of the midline. HALDN with a Pfannenstiel incision will be performed by placing the donor in the French position. A four-port transperitoneal approach will be used: a 10-mm umbilical trocar for the laparoscope, one 5-mm port in the midline, one 12-mm port at the level of the umbilicus to the left/right of the midline, and an additional 5-mm port will be inserted at the left/right border of the Pfannenstiel incision. As soon as the blood vessels are divided and the nephrectomy is completed, the graft will be extracted using the hand port. At the end of the operation, an abdominal drain will be placed and the wound will be closed.

### Modification of the protocol

Protocol amendments will be considered by the principal investigator after feedback from the Clinical Trial Center. All protocol amendments will be submitted to the Ethics Committee for approval. No further recruitments will take place until the modifications are accepted.

### Assessment of safety and termination criteria

To assess the safety of the periumbilical and Pfannenstiel approaches, serious adverse events (SAEs) will be observed and evaluated. Only intervention-related events that occur during surgery and follow-up will be documented. At each visit, the physician will ask the donor if he/she has suffered from any SAEs since the last visit. The attending physician must tell the principal investigator about any reported SAEs within 24 h. The report will be complete and include details of the SAE and whether the SAE was caused by the trial treatment. All intervention-related SAEs will be documented and analyzed.

Donors will be excluded from the study if they withdraw their consent to participate in the trial. A donor may withdraw consent at any time without explanation and without affecting further medical care. The principal investigator may terminate the trial at any time in consultation with the key research associates and the biostatistician. Possible reasons for termination include high morbidity or mortality rates and any indication of potential health hazards caused by either the study treatment or external factors.

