### Randomization and blinding

Donors will be randomized to the different groups using the block randomization method. Each block contains two groups of periumbilical and Pfannenstiel incisions. The block size is hidden from the trial executers and clinicians. Possible balanced combinations of these groups within the block are numbered consecutively. Then, blocks are randomly chosen using simple randomization software (Microsoft Excel®), and a series of randomly assigned periumbilical and Pfannenstiel incisions are generated based on the random sequence of blocks. Allocation will be concealed using sequentially numbered, sealed opaque envelopes prepared by a member of our Clinical Trial Center. Donors will be randomly allocated to either the control arm (periumbilical incision, Group A), or the intervention arm (Pfannenstiel incision, Group B) a day before surgery. The trial executors receive randomly generated treatment allocations within sealed opaque envelopes. Afterwards, medical staff will personally inform the expert surgeon as to which treatment group the patient has been randomized. To avoid any potential prediction of group allocation, information on the block length will be kept away from the study site.

After the operation, the periumbilical and hypogastric regions will be covered with a double wound dressing until discharge. During this period, the severity of pain, rescue analgesic, and PEFR will be evaluated by anesthesiologists blinded to the incision type. Participants will also be blinded to the incision type. If blinding could affect the patient’s treatment, for example in the case of a medical emergency or serious medical condition, then the participant/assessor will be unblinded. After POD 4, a nephrologist who is unaware of the study will evaluate and document the primary and secondary endpoints of the trial. At the end of the trial, the data management center will receive all sealed envelopes and will check the accuracy of randomization numbers.

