One limitation of this RCT is that the primary endpoint cannot be evaluated blind. However, some early outcome measures will be evaluated double blindly (participant and assessor blinded) until discharge by covering both periumbilical and hypogastric areas using double wound dressing. Furthermore, to prevent bias in further assessments, all follow-up visits will be performed by a nephrologist who is unaware of the study. Another limitation is that the primary outcome of this RCT is a subjective, self-maintenance measure. However, results of the Katz ADL self-administered questionnaire are known to be valid and reliable [27]. In addition to the Katz ADL questionnaire, we will also use the established IPAQ-SF [28], which will be completed by the investigator before and after surgery. There is no data monitoring process in the HAPERPACT trial, because the methods used are both standard surgical procedures for living donor nephrectomy and also because the biggest part of documentation in this trial is the standard clinical follow-up of the patients. Therefore, a data monitoring committee is dispensable in this trial.

In summary, published retrospective and non-randomized prospective studies have not clarified the advantages and disadvantages of periumbilical versus Pfannenstiel incisions in HALDN. The HAPERPACT trial will be the first RCT to compare the outcome of HALDN using two different types of incision. The comprehensive findings of this study may help to decide the optimal nephrectomy procedure for earlier return to normal physical activity, comfort, and satisfaction in donors as well as graft function in recipients.

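### Documentation and analysis of SAEs are limited to events judged intervention-related, with no blinded causality assessment specified, although any SAE must be reported

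*Protocol article*

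**What the plan says.** The section "To assess the safety of the periumbilical and Pfannenstiel approaches, serious adverse events (SAEs) will be observed and evaluated" opens with this purpose: SAEs serve to assess the safety of both approaches. It then restricts the record: "Only intervention-related events that occur during surgery and follow-up will be documented". It closes with the matching analysis rule: "All intervention-related SAEs will be documented and analyzed".

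Between these sentences it sets a wider reporting duty. The physician asks about SAEs at every visit, and "The attending physician must tell the principal investigator about any reported SAEs within 24 h". The report must "include details of the SAE and whether the SAE was caused by the trial treatment".

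On blinding, the section on randomization and blinding says that, until discharge, "the severity of pain, rescue analgesic, and PEFR will be evaluated by anesthesiologists blinded to the incision type". Causality of SAEs is not among the blinded assessments. After postoperative day 4, a nephrologist who does not know of the study assesses the primary and secondary endpoints.

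Table 1 separately defines safety endpoints that carry no relatedness condition: any intraoperative complication, a list of postoperative surgical and medical complications graded by Clavien-Dindo, incisional hernia, and death from any cause during follow-up.

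**The concern.** Whether an SAE is kept depends on a judgement made after randomisation. An SAE table restricted in this way compares events that someone attributed to the intervention, which is not the same as events that occurred in each arm. If attribution differs by arm, the table can show a difference that does not exist or hide one that does. If attribution does not differ, it still understates how often donors had an SAE.

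The statistical analysis plan cannot repair this later, because an event that was never documented cannot be tabulated. The trial is small and its participants are healthy people operated on for someone else's benefit, so each SAE counts. The Discussion also states that "There is no data monitoring process in the HAPERPACT trial", so no committee looks independently at the events left out.

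**Working it through.** **1. The rules side by side (safety and termination section)**

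| Step | Scope stated |
|---|---|
| Question at each visit | any SAE |
| Report to the principal investigator | any reported SAE, with details and causation |
| Documentation | intervention-related only |
| Analysis | intervention-related only |

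The causation statement makes sense only if unrelated SAEs are reported too. The information therefore reaches the trial, and the documentation rule then leaves part of it out. Read literally, the restricting sentence speaks of events in general, which would also collide with the Table 1 entry for intraoperative complications. In context it most likely means SAEs.

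**2. Who assesses causation**

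The attending physician reports to the principal investigator. The blinding status of neither is stated. Three statements suggest that the allocation may be known: "medical staff will personally inform the expert surgeon as to which treatment group the patient has been randomized"; a serious medical condition may lead to unblinding; and the dressing hides the incision only until discharge. None of them says that the person assessing causation is unblinded.

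**3. Which events can be lost**

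- Intraoperative complications: kept in Table 1.
- Listed postoperative complications and incisional hernia: kept.
- Deaths: kept, whatever the cause.
- Non-fatal postoperative SAEs outside the list and judged related: kept through the SAE rule.
- Non-fatal postoperative SAEs outside the list and judged unrelated: lost.

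The medical part of the list names pneumonia, pleural effusion and urinary tract infection. A postoperative thromboembolic or cardiac event, for example, is not named.

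**4. Possible size in the SAE table**

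The arm size is the plan's own: 22 / (1 − 0.15) = 25.9, rounded up to 26 per arm, and 2 × 26 = 52. The plan gives no SAE figure to reproduce, so the SAE risks and the shares judged related below are assumptions.

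Expected SAEs per arm = 26 × p, with the same true risk p in both arms. Expected recorded SAEs = 26 × p × q, where q is the share judged related.

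| p | True SAEs per arm | Recorded, q = 0.5 in both | Recorded, q = 0.5 v 0.8 |
|---|---|---|---|
| 5% | 1.3 | 0.65 v 0.65 | 0.65 v 1.04 |
| 10% | 2.6 | 1.30 v 1.30 | 1.30 v 2.08 |
| 20% | 5.2 | 2.60 v 2.60 | 2.60 v 4.16 |

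The apparent risk ratio is the ratio of the two shares, since p cancels: 0.5/0.5 = 1.0 with equal attribution, 0.8/0.5 = 1.6 with unequal attribution, and 0.5/0.8 = 0.62 if the direction is reversed. At a more extreme 0.3 v 0.9 it is 3.0. In whole events, also assumed: with 4 SAEs in each arm (4/26 = 15.4%), judging 2 unrelated in one arm only leaves 2/26 = 7.7% there. These figures describe the SAE table alone. Any of these events that are also Table 1 complications or deaths remain in that comparison.

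**The case against.** The strongest defence is that the events most plausibly tied to the incision are already covered. Wound infection, seroma, haematoma, hernia, burst abdomen, bleeding, abscess and ileus are all listed in Table 1, with no relatedness filter. This stands. A reader might infer that the whole between-arm safety comparison is filtered through attribution, and the documents do not support that.

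Second, a reader might infer that the judgement is an unblinded one. That too goes beyond the text, which does not state the assessor's blinding status. The Discussion has all follow-up visits done by a nephrologist unaware of the study, and the data management section has the CRF completed by an investigator who did not evaluate the patient. These safeguards are partial. The nephrologist's stated task is the endpoints, and someone unaware of the study is poorly placed to say whether the trial treatment caused an event. What can be said is that no blinded causality assessment is specified.

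Third, it is tempting to conclude that the person who can stop the trial sees only related events. The reporting rule says otherwise, since any reported SAE goes to the principal investigator, and the stated reasons for termination extend to external factors. The loss is in the record and the analysis.

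Fourth, the article does not define relatedness, although both arms undergo a nephrectomy and differ in the hand-port approach. The full protocol may hold that definition, so its absence here is not counted against the plan.

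**Conclusion.** The point holds in limited form. The article states twice, as a rule, that SAE documentation and analysis cover only intervention-related events. This conflicts with its own duty to report any SAE with a view on causation, and no blinded causality assessment is specified. Condensation into an article does not explain it, because the restriction is written out.

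The loss is mainly non-fatal postoperative SAEs outside the Table 1 list that are judged unrelated. The SAE comparison is biased only if attribution differs between arms; otherwise it is incomplete. The apparent ratios of 1.6 or 0.62 rest wholly on assumed attribution shares of 50% and 80% and say nothing about what will happen. The primary endpoint and the sample size are not affected.

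**What to change.** In the safety and termination section, replace the two restricting sentences so that every SAE from surgery to postoperative week 8, the last scheduled visit, is documented whatever its attribution. Record relatedness as a separate CRF field. Tabulate all SAEs by randomised arm first and the related subset second. Align the wording with the sentence on reporting any SAE, so that reporting, documentation and analysis share one scope.

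The cost is a small change of text, one CRF field and a few more SAE records in 52 donors. Since any SAE is already to be reported with a statement on causation, little new information has to be collected. As a protocol amendment the change goes to the Ethics Committee, and the article's own rule suspends recruitment until a modification is accepted.

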### Randomization and blinding

Donors will be randomized to the different groups using the block randomization method. Each block contains two groups of periumbilical and Pfannenstiel incisions. The block size is hidden from the trial executers and clinicians. Possible balanced combinations of these groups within the block are numbered consecutively. Then, blocks are randomly chosen using simple randomization software (Microsoft Excel®), and a series of randomly assigned periumbilical and Pfannenstiel incisions are generated based on the random sequence of blocks. Allocation will be concealed using sequentially numbered, sealed opaque envelopes prepared by a member of our Clinical Trial Center. Donors will be randomly allocated to either the control arm (periumbilical incision, Group A), or the intervention arm (Pfannenstiel incision, Group B) a day before surgery. The trial executors receive randomly generated treatment allocations within sealed opaque envelopes. Afterwards, medical staff will personally inform the expert surgeon as to which treatment group the patient has been randomized. To avoid any potential prediction of group allocation, information on the block length will be kept away from the study site.

After the operation, the periumbilical and hypogastric regions will be covered with a double wound dressing until discharge. During this period, the severity of pain, rescue analgesic, and PEFR will be evaluated by anesthesiologists blinded to the incision type. Participants will also be blinded to the incision type. If blinding could affect the patient’s treatment, for example in the case of a medical emergency or serious medical condition, then the participant/assessor will be unblinded. After POD 4, a nephrologist who is unaware of the study will evaluate and document the primary and secondary endpoints of the trial. At the end of the trial, the data management center will receive all sealed envelopes and will check the accuracy of randomization numbers.

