## Methods/design

### Setting

This is a single-center, expert-based RCT. The trial is now underway at the Division of Transplantation Surgery, Department of General, Visceral, and Transplantation Surgery, University of Heidelberg. It was initiated in November 2017, and it is expected to progress for 2 years. The trial was registered at ClinicalTrials.gov under registration number NCT03317184 on October 23, 2017. The Standard Protocol Items: Recommendations for Interventional Trials (SPIRIT) checklist is provided in Additional file 1.

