### Patient recruitment

The study protocol was accepted by the independent Ethics Committee of the University of Heidelberg (registration number S-291/2017). As shown in the study flow chart (Fig. 1), all kidney donors (including left and right kidneys) are currently being screened for eligibility criteria. To be eligible for the study, living donors must be more than 20 years of age and must not be receiving permanent pain therapy. Only donors with a single artery and vein in the graft are being enrolled in this trial. Donors with infections or scars in the periumbilical or hypogastric area, bleeding disorders, chronic use of immunosuppressive agents, and active infection are being excluded. All included donors will be informed about periumbilical and Pfannenstiel incisions for HALDN, as well as their potential benefits and side effects. Eligible donors will receive a written informed consent form. Donors who sign the informed consent form will be included in the study. Reasons for exclusion from the Hand-Assisted laparoscopic donor nephrectomy PERiumbilical versus Pfannenstiel incision and return to normal physical ACTivity (HAPERPACT) trial will be documented and explained in the screening form. After baseline assessments and assessment of eligibility, the patient will be randomized to the periumbilical or Pfannenstiel arm.

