### Statistical methods

#### Sample size

The null hypothesis is that Pfannenstiel incision is not superior to periumbilical incision in terms of the average number of days it takes the donor to return to normal physical activity in the 4 weeks after surgery. We chose 10 days difference in return to normal physical activity as the minimal clinically important difference, because a difference of less than 10 days is not valuable enough to decide the standard surgical method. Therefore, we used a difference of 10 days for sample size calculation. The standard deviation is expected to be 13 days, according to the results of El-Galley et al. [15], who compared days to return to work between periumbilical and Pfannenstiel incision groups. However, we chose “days to return to normal physical activity” as the primary endpoint rather than “days to return to work” because the nature of patients’ work and their capabilities are different, and some of our living donors may be unemployed or housekeepers. A one-sided significance level of α = 0.05, a power of 80%, and a sample size of 44 patients (22 per group) are required to apply a two-sample *t* test (calculations performed with AddPlan 6.0). To account for a 15% drop-out rate, 26 patients will be enrolled in each study arm (52 patients in total).

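### Withholding the block length does not prevent prediction of the next arm when one centre uses balanced blocks and the surgeon learns every allocation

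*Protocol article*

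**What the plan says.** The section Randomization and blinding describes block randomization with two arms per block. On how the sequence is built it says: "Possible balanced combinations of these groups within the block are numbered consecutively". Blocks are then drawn at random to form the list. On secrecy it says "The block size is hidden from the trial executers and clinicians", and later gives the purpose: "To avoid any potential prediction of group allocation, information on the block length will be kept away from the study site".

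The other relevant statements are:
- Concealment: "Allocation will be concealed using sequentially numbered, sealed opaque envelopes prepared by a member of our Clinical Trial Center".
- Knowledge of the arm: once the envelope is opened, "medical staff will personally inform the expert surgeon as to which treatment group the patient has been randomized". Allocation takes place the day before the operation.
- Centres (Setting): "This is a single-center, expert-based RCT". No stratification is described, so there is one running sequence.
- Order of events (Patient recruitment): "After baseline assessments and assessment of eligibility, the patient will be randomized to the periumbilical or Pfannenstiel arm". Consent also comes before allocation.
- Size (Sample size): "26 patients will be enrolled in each study arm (52 patients in total").

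**The concern.** Sealed envelopes hide the list. They do not hide what can be deduced from allocations already made. In a comparison of incisions the surgeon must know each arm. With one centre and one sequence, the local team can keep a running count. Balanced blocks pull that count back to equality, so the arm that is behind is more likely to come next, whatever the block length.

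Anyone who holds such a guess before a donor is approached, or before the operating list is ordered, could let it influence who enters next. Sealed envelopes and an intention-to-treat analysis do not remove that kind of selection bias. The primary endpoint is self-reported, and the Discussion concedes that it cannot be assessed blind. With 52 donors, a modest amount of steering could matter.

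**Working it through.** **Inputs.** From the article: 1:1 balanced blocks, one centre, surgeon told each arm, 52 donors, SD 13 days, 22 evaluable donors per group, one-sided 5% t test. The article gives no block length and no predictability figure, so there is nothing of its own to reproduce on this point. Lengths 2 to 8 are assumed.

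**1. Length 4 by hand.** The six balanced blocks are AABB, ABAB, ABBA, BBAA, BABA and BAAB.
- *Certain allocations (length known).* AABB and BBAA fix their last two places; the other four fix only the last. (2×2 + 4×1)/(6×4) = 8/24 = 33.3%, or about 17 of 52.
- *Guessing the arm that is behind (coin toss when tied).* Place 1: 0.5. Place 2: 2/3. Place 3: 1/3×1 + 2/3×0.5 = 2/3. Place 4: 1. Mean = (0.5 + 0.667 + 0.667 + 1)/4 = 70.8%.

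**2. General fixed length b = 2m.**
- Certain share = 2/(b + 2).
- Correct guesses = 1/2 + [4^m / C(2m, m) − 1]/(2b).

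| b | Certain if length known | Correct guesses |
|---|---|---|
| 2 | 2/4 = 50% | 0.5 + (4/2 − 1)/4 = 75.0% |
| 4 | 2/6 = 33.3% | 0.5 + (16/6 − 1)/8 = 70.8% |
| 6 | 2/8 = 25% | 0.5 + (64/20 − 1)/12 = 68.3% |
| 8 | 2/10 = 20% | 0.5 + (256/70 − 1)/16 = 66.6% |

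These hold for complete blocks. A simulation of 52 donors, with a guesser who sees only the running arm counts, gives 75.0%, 70.8%, 67.7% and 65.9%. Lengths 6 and 8 come out slightly lower because the last block is cut short.

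**3. Can a fixed length be inferred?** Take candidates 2, 4, 6 and 8 and a true length of 4. The smallest length consistent with the observed sequence is 4 in about 56% of simulated runs after 8 donors and about 82% after 16.

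**4. Does 26 per arm reveal the length?** The even divisors of 52 are 2, 4, 26 and 52. However, 26 is simply 22 inflated for 15% drop-out: 22/0.85 = 25.9, rounded up to 26. It is an enrolment target. Nothing says that the list ends at 52 or that the last block is complete, so 6, 8 or a mixture also fits the text.

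**5. Randomly varied lengths (52 donors, simulated).** The certain share is for a guesser who knows which lengths are in the mix, drawn with equal probability.

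| Lengths | Certain | Correct guesses |
|---|---|---|
| fixed 4 | 33% | 70.8% |
| 2, 4, 6 | about 4% | 70.1% |
| 4, 6, 8 | about 2% | 67.7% |
| simple randomization | 0% | 50% |

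Variation removes most certainty but barely moves the guess rate. The 4/6/8 mix left a final arm difference of at most 4 donors (mean 0.55). Simple randomization left a mean difference of about 6.

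**6. Illustration of the stakes.** The amount of steering here is assumed and is not in the article. Suppose donors entered on a guess differ in expected recovery by δ days in the direction of the guess. With guess rate g, the false arm difference is 2δ(2g − 1). At length 4 this is 2δ × 0.417: 0.83, 1.67 or 2.5 days for δ = 1, 2 or 3. With 22 per arm, SD 13 and no true effect, the simulated one-sided error is about 7%, 11% or 15% instead of 5% if the steering favours Pfannenstiel. Under the 4/6/8 mix it is about 7%, 10% or 13%.

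**The case against.** The strongest reply is that this is a conventional design with conventional safeguards: a hidden block size, numbered opaque envelopes prepared by the Clinical Trial Center, consent and eligibility settled before allocation, and allocation only on the day before surgery. A public article would not be expected to reveal the block length. Several stronger readings also fail:

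- *That the length is fixed.* A reader might infer this from the singular wording and the single numbered list of combinations. It is a strong inference, but the text does not state it.
- *That the length must be 2 or 4, and can be worked out from the published protocol.* This treats the enrolment target as a property of the list, which it is not (step 4).
- *That selection is taking place.* No section says that those who learn past arms also screen, consent or schedule donors. By the day before surgery the case has probably been booked.
- *That fixed length is the main cause.* It is not. Small balanced blocks with known past allocations drive the guess rate, and varying the length changes it little (step 5).

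All of this limits the point but does not remove it. The safeguards protect the list, whereas a guess uses only past allocations and can be made before a donor is approached. The article need not disclose a length, but it does claim that withholding it avoids any prediction, and that claim is wrong for every length examined.

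**Conclusion.** The point holds in a limited form. Hiding the block length does not deliver the protection claimed for it. For fixed lengths from 8 down to 2, a simple guess is right about 66% to 75% of the time without knowing the length. If the length is inferred, about 20% to 50% of allocations are certain (33% at length 4). These figures assume a fixed length, which the text suggests but does not state, and a team that keeps track of past arms. Whether this becomes bias depends on whether those people influence enrolment or scheduling, on which the article is silent. It is an opportunity for selection bias, and nothing in the document shows that bias has occurred. The sample size calculation is unaffected. The change is worth making because it removes nearly all certain predictions at small cost.

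**What to change.** If the block length is fixed, the Clinical Trial Center should generate the remaining envelopes with block lengths varied at random, leaving out length 2 (for example 4, 6 and 8). The final split should be allowed to differ from exactly 26 per arm. The sentence claiming to avoid prediction should be replaced by a description of this method, without listing the lengths used. If lengths already vary, only that sentence needs changing.

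This is a partial fix: certain predictions fall to about 2%, but the guess rate stays near 68%. Keeping enrolment and list order out of the hands of staff who know past arms would address what remains, and the protocol could say whether this is already so.

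The cost is a new set of envelopes, a possible final imbalance of a few donors with little loss of precision, and an amendment. Under Modification of the protocol, amendments go to the Ethics Committee and recruitment stops until they are accepted. Trial status says that the trial is recruiting, so the change would pause enrolment and could protect only donors not yet randomized.

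### The blinding dressing leaves out an upper-quadrant port site that only the periumbilical arm has, so the blinding claimed until discharge is not secured for pain, rescue analgesic use and peak flow

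*Protocol article*

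**What the plan says.** In the protocol article, the section Randomization and blinding describes the mask: "After the operation, the periumbilical and hypogastric regions will be covered with a double wound dressing until discharge". It adds that during this period anesthesiologists who do not know the incision type assess pain severity, rescue analgesic use and peak expiratory flow rate (PEFR), and that participants are blinded too.

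The Discussion rests its claim on the same device. It says that "some early outcome measures will be evaluated double blindly (participant and assessor blinded) until discharge", and that this is achieved "by covering both periumbilical and hypogastric areas using double wound dressing". Neither section mentions a port site.

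The section Standardized therapy and trial interventions gives the arms different port layouts. For the periumbilical arm: "A 5-mm laparoscope port will be placed at the midclavicular line in the left/right upper quadrant", about two fingers below the ribs, and "one working instrument (12 mm) will be placed at the level of the umbilicus to the left/right of the midline". For the Pfannenstiel arm: "a 10-mm umbilical trocar for the laparoscope, one 5-mm port in the midline, one 12-mm port at the level of the umbilicus", again beside the midline, with a fourth 5-mm port at the edge of the Pfannenstiel incision.

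**The concern.** A dressing conceals the arm only if it hides every mark that differs between the arms. Here the two dressed regions correspond to the two hand-port incisions, while the operations also differ in where the smaller ports go. A mark that occurs in one arm only and lies outside the dressed area can identify the arm even when both main incisions are hidden.

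The outcomes at stake are the ones the article presents as blinded until discharge: pain on the visual analog scale (VAS), rescue analgesic use and PEFR. VAS is the donor's own report and PEFR depends on the donor's effort, so both are open to expectation in the donor or the assessor. The Discussion also offers this early blinding as a partial answer to its admission that the primary endpoint cannot be assessed blind, so the claim carries some weight in how the trial will be read.

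**Working it through.** No figure in the article bears on this point, so the check sets the wound sites against the dressed area. The sites come from Standardized therapy and trial interventions. The dressed area comes from Randomization and blinding and from the Discussion, which agree.

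| Site | Periumbilical arm | Pfannenstiel arm | Within a named dressed region? |
|---|---|---|---|
| Hand-port incision | Midline periumbilical | Pfannenstiel | Yes, in both arms |
| Umbilicus | Within the incision region | 10-mm port | Yes |
| Umbilical level, beside the midline | 12-mm port | 12-mm port | Not clear, but the same in both arms |
| Midline | None besides the incision | 5-mm port, height not stated | Cannot be determined |
| Edge of the Pfannenstiel incision | None | 5-mm port | Taken as yes (beside the hypogastric incision) |
| Upper quadrant, midclavicular, below the ribs | 5-mm port | None | No |

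Step by step:

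1. The 12-mm port beside the midline occurs in both arms, so it reveals nothing whether covered or not.
2. The upper-quadrant port occurs in the periumbilical arm only. A site just below the ribs in the midclavicular line is neither periumbilical nor hypogastric. If the text is followed as written, it is outside the mask.
3. A small plaster on that port would not solve this. Unless the Pfannenstiel arm receives the same plaster at the same place, the plaster itself marks the arm. The article provides no such sham.
4. The mark informs only someone who knows both layouts. The anesthesiologists work at a single center where, according to the Discussion, both techniques are standard, so it is reasonable to suppose that some could recognise the site. Patient recruitment says donors are told about both incisions and their benefits and side effects. It does not say they are told the port sites, so recognition by donors is possible but less certain.
5. The outcomes affected are those assessed up to discharge under the blinding claim: VAS pain, rescue analgesic use and PEFR. Statistical analysis gives secondary outcomes p values of a descriptive kind only, so no confirmatory test depends on them.

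**The case against.** The best defence is that unmasking is inferred, not shown. Rating pain, counting analgesics and measuring peak flow do not require exposing the abdomen, and the article does not say whether the assessors look at the wounds or know the layouts. This stands, and it limits the point to blinding that is not secured, as opposed to blinding that is known to fail.

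A second defence is that a journal article condenses, so dressing size and port-site plasters may be settled in the full protocol. A very large dressing might also reach the subcostal site. This does not remove the point. The article names the covered regions twice, in the same terms, and rests the blinding claim on them. What it specifies falls short of its own description of the ports.

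Four stronger readings are tempting, and the documents do not support them:

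- *That donors and assessors will see the arm in all 52 cases (26 + 26).* This is only a ceiling. It needs every observer to know both layouts, to look, and, for Pfannenstiel donors, to reason from the absence of a mark.
- *That the midline port in the Pfannenstiel arm is a second uncovered mark.* Its height is not given, so it may lie under either dressing.
- *That the primary endpoint is newly compromised, because the daily diary starts in hospital.* The Discussion already lists the lack of blind assessment of the primary endpoint as a limitation.
- *That bias would favour the Pfannenstiel arm as the new technique.* The article treats both incisions as standard. Its Background cites earlier studies favouring the periumbilical incision for pain and the Pfannenstiel incision for wound complications and cosmetic result. No direction follows.

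**Conclusion.** The point holds in limited form. The mask as written leaves one arm-specific mark uncovered, the subcostal midclavicular port of the periumbilical arm. The participant and assessor blinding claimed until discharge is therefore not secured for VAS pain, rescue analgesic use and PEFR.

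This rests on two assumptions: that the dressings cover the two named regions and no more, and that at least some assessors or donors know the port layouts and could see the site. The frequency of unmasking, and the direction and size of any bias, cannot be determined from the documents. The consequence is confined to secondary outcomes analysed descriptively. The sample size and the primary analysis are unaffected. The change is still worth making, because it is cheap and protects a claim on which the article relies.

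**What to change.** In both arms, apply the same set of opaque dressings until discharge over every incision and port site used in either technique: the upper quadrant on the operated side, the umbilicus, the midline, the site beside the umbilicus, and the suprapubic area including the edge of the Pfannenstiel incision. State this in Randomization and blinding and repeat it in the Discussion. Optionally, record at discharge which arm the donor and the assessor believe was used. This is good practice for judging whether the mask worked, but its absence is not an error.

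If the dressings are not changed, state that blinding of VAS pain, rescue analgesic use and PEFR may be incomplete. Calling these outcomes unblinded would go too far, because the main incisions would still be covered.

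The cost is a few extra dressings per donor and, if adopted, one question. The article describes the trial as still recruiting, and its section on modification of the protocol gives the route for an amendment. That section halts further recruitment until the Ethics Committee accepts a change, so a short pause should be expected. Correcting only the wording of the blinding claim in the final report needs no change to donor procedures.
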